## Study procedures

To achieve the goals of this project parallel study procedures for each aim will be conducted throughout the project period.

### Implementation and needs assessment procedures

The implementation approach is modeled after the Exploration, Preparation, Implementation, Sustainment (EPIS) implementation science framework [33]. EPIS allows for examination of a change process at multiple levels, across time, and through four successive phases: Exploration, assessing system, organization, provider, and client-level factors that explain service gaps and potential barriers/facilitators for change; Preparation, using that awareness to develop plans for enhanced delivery of each approach; Implementation, training of practices to be adopted; and Sustainment, maintaining the use of the PN and MHU approaches. In each phase, EPIS identifies factors relevant to implementation success in the inner context (within the implementing organization\community itself), outer context (external to, but still influential on, the implementing organization\community), and their interactions [34–37].

A planned Needs Assessment Survey (NAS) will be distributed prior to initiating the two intervention arms and will be repeated annually throughout the project period in each of the four communities documenting treatment referral and linkage processes within the participating communities. The online survey inquiries about existing relationships and referral patterns among justice agencies, medical service providers, and community health providers. NAS participants will include representatives from key stakeholder agencies in each community. These agencies will include prisons and jails, community corrections agencies, county or city health departments, substance use treatment agencies, and HIV service agencies. NAS results are critical for helping to inform the details of the two interventions in each of the four communities.

Upon review of the NAS results, focus groups with a subset of the NAS study population from all four communities will be conducted. The purpose of the focus groups is to collect in-depth qualitative data on the current services provided along the continua of care for HIV, SUD, and HCV. Focus group facilitators (i.e., researchers) will utilize semi-structured questions to allow members to discuss barriers to services delivery and uncover gaps in patient care moving through services among local networks, with emphasis on the implementation challenges and potential solutions for PN programs and MHU service provision. The focus group (qualitative) questions will thematically correspond with NAS (quantitative) measures, allowing ease in triangulation [38] to evaluate if these two data sources align on key pieces of information. Thus, findings from the NAS and focus group both will inform the gaps needed to be addressed by both intervention arms.

Audio focus group recordings will be transcribed and qualitatively coded by at least two research staff. Coding fidelity and data reliability will be addressed with inter-coder exercises to achieve coding agreement [39] when applying primary codes in the official transcripts. With ATLAS.ti [40], transcripts will be coded using a deductive approach [41], to identify primary themes and refined secondary themes [39]. For example, the main code, “communication” will have secondary codes (“inter-agency" and “intra-agency “) to explore more nuanced levels of information flow between and within agencies. Through an iterative process of coding and team debriefings, a consensus approach will be used to control coder bias and shared common understanding of phenomena [34, 42].

### Feasibility and acceptability procedures

Primary implementation outcomes include feasibility (health care utilization impact among justice-involved individuals, contributions of interagency workgroup members on primary outcomes); acceptability (participant satisfaction, perceived usefulness); sustainment (continued utilization), and costs required to implement and sustain the approaches and to scale-up in additional communities. Additional outcomes will examine broader community health care impacts including other health services accessed, expanded opioid use disorder (OUD)/SUD services [43], and common barriers (e.g., stigma) to service access across the community provider spectrum. Given the growing concern regarding overdose and injection-related HIV risk behaviors [1, 15, 44–48] an examination of people who inject substances will focus on gaining insight into participant and social context (inner and outer) factors associated with the effectiveness outcomes.

### Randomized controlled trial procedures

#### Recruitment and screening

Recruitment of participants will occur from multiple facilities and settings serving justice-involved individuals. Participants in Dallas and Tarrant counties will primarily be recruited from health care and substance use treatment facilities where persons involved in the justice system receive care. Connecticut-based participants from both project sites will primarily be recruited from the Connecticut Department of Correction prior to release from incarceration in prison and jail. Sites will also recruit from community-based organizations providing services to justice-involved persons who use or used substances and/or are living with or at risk for HIV. Furthermore, adapted snowball sampling will be utilized for community based referrals [49]. After full enrollment in the project, participants will be provided with recruitment vouchers to refer persons in the community they believe may be eligible for the project. Participants will be compensated in the amount of $20 per referral for up to three [3] people who are successfully enrolled in the project. Potential participants will be approached by experienced research staff who received formal training in the administration of all study procedures and interview questionnaires by qualified trainers. Participants who meet preliminary eligibility criteria (including age, ability to speak English and/or Spanish, and current or recent justice involvement) and state clear interest in study participation, will then be invited to voluntarily complete the screening informed consent process with study staff.

#### Eligibility, informed consent, and enrollment processes

Once a participant meets all the pre-screen inclusion criteria and screening informed consent has been completed, the participant will begin the three-part enrollment process. The three parts include: (1) determining study eligibility; (2) providing written informed consent for the full project, which includes the successful completion of the consent questionnaire; and (3) completing all baseline measures (Table 1. Project Assessment and Timeframes). Once the baseline assessments have been completed, the participant will be considered fully enrolled, and will then be randomized. For those in justice settings where biological assessments cannot be completed at the time of the baseline interview, participants will be randomized after the baseline interview assessments have been completed, and biological assessments will be conducted upon release to the community. Enrollment status and study data or results will not be shared with judicial or correctional authorities, unless specifically authorized by the participant.

**Table 1 Tab1:** Project assessment and timeframes

Study procedures	Intervention period (Day of Release/Randomization-Month 6)				Post-Intervention
	Baseline	Month 1	Month 3	Month 6	Month 12
Activity and biological tests					
Project screening	X				
Consent & randomization	X				
HIV rapid test or viral load based on status	X			X	X
Hepatitis C rapid test or viral load based on status	X			X	X
Sustained preexposure prophylaxis/antiretroviral therapy adherence (dried tenofovir blood spot)				X	
Urine tenofovir			X	X	X
Urine substance use toxicology	X		X	X	X
Testing for sexually transmitted infections (gonorrhea, chlamydia, hepatitis B, and syphilis)	X			X	
Interview assessments					
Demographics	X				
HIV risk behaviors	X		X	X	X
Timeline followback (self-reported daily opioid and stimulant use)	X		X	X	X
Patient Reported Outcome Measurement Information System (PROMIS) for Quality of Life	X		X	X	X
Patient Health Questionnaire (PHQ9; depression)	X		X	X	X
Visual Analog Scales (VAS) for antiretroviral therapy/preexposure prophylaxis/medication for opioid use disorder adherence		X	X	X	X
Texas Christian University (TCU) Drug Screen	X		X	X	X
Engagement in care (prescription refill for preexposure prophylaxis, antiretroviral therapy, medication for opioid use disorder)		X	X	X	X
Overdose and adverse events		X	X	X	X
Craving for opioids and stimulants	X		X	X	X
Incentives*	$50	$50	$50	$75	$75

^*^Participants will also receive payment of $5 for monthly check-ins on months where no research interviews are being conducted

#### Eligibility criteria

Inclusion criteria are as follows:

(1) Age 18 or older; (2) able to provide written informed consent in English or Spanish; (3) currently in a justice supervised facility (e.g., jail, prison, treatment center, or halfway house) with pending release date within 30 days or involvement with the justice system within the last 30 days (e.g., arrest, probation, parole, or incarceration); (4) willing to have HIV testing to determine status, or confirmed to be living with HIV by a medical chart review; (5) having a pre-custody history of opioid and/or stimulant use within 12 months prior to incarceration; (6) having a pre-custody history of condomless sexual intercourse and/or injection substance use within six months prior to custody; and (7) be willing to learn about PrEP if not living with HIV.

Exclusion criteria are as follows:

(1) Not remaining in the local area after release from custody; (2) having a severe medical or psychiatric disorder making participation unsafe; (3) being released to inpatient care facility; and (4) exhibiting behavior that may have a potential risk to research staff.

#### Post enrollment

Upon completion of the enrollment process, including screening, written informed consent, baseline assessment, and randomization, participants will undergo assessments at months 1, 3, 5 and 12. The following biological tests will be completed at baseline, and months 6 and 12: HIV rapid test or viral load based on status, HCV rapid test or viral load based on status, and testing for STIs (gonorrhea, chlamydia, hepatitis B, and syphilis). To assess for adherence to tenofovir based ART or PrEP medications, urine and a dried blood spot (DBS) will be analyzed at months 3, 6 and 12. Urine toxicology screens will be conducted to assess substance use at baseline and months 3, 6, and 12. Items in the follow-up interview assessments will include: demographic characteristics, sexual and injection HIV risk behaviors, daily opioid and stimulant use and route via the timeline followback, engagement in medical, substance use and social services or treatments, quality of life and pain via the Patient Reported Outcome Measurement Information System (PROMIS), depression symptoms using the Patient Health Questionnaire (PHQ9), TCU Drug Screen 5, craving for opioids and stimulants, and overdose experiences. At each follow-up study visit participants will be asked to complete a medical release of information for community-based providers to allow project staff to verify attendance of medical visits as well as prescription receipt.

#### Participant tracking

At each study visit participants will be asked to provide extensive locator information including a mailing address, phone number, social media contact information, hang out locations, and place of work. If we are not able to contact the participant directly, participants are also asked to provide contact information for a friend or family member as an alternative contact. Project staff will use this information for appointment reminders and to maintain contact with the participant between appointments. If a participant is not able to be contacted project staff will conduct community outreach to the addresses and locations provided. If participants are re-incarcerated during their time in the study, IRB approval and agreements with local correctional facilities have been obtained to allow research staff to follow and interview participants while incarcerated.

## Covariate and outcome measures

Measures used to assess eligibility and intervention effectiveness are listed in Table 1 and described below. There will be a total of five research-related visits conducted in this project, including at the time of baseline and enrollment, during the intervention period at months 1, 3 and 6 post-release/enrollment, and the final visit 6 months post-intervention (12 months post-release/enrollment; Fig. 2). Interview based data will be collected using REDCap interview software.

**Fig. 2 Fig2:**
[figure not shown]
Participant flow through project

### Demographic, medical diagnosis, and treatment history

At the time of the baseline assessment demographic characteristics including age, gender, race, ethnicity, housing status, income, and education will be collected. Participants will also be asked about their pre-justice involvement behavior and medical history. Self-reported medical history includes previous diagnosis and treatment of HIV, HCV, sexually transmitted infections (STIs), and other medical diagnoses. HIV and HCV diagnoses will be confirmed through medical chart request. Follow-up assessments include items to assess the change in housing status, income, justice involvement, and new medical diagnoses.

### Healthcare initiation, adherence, and retention of care

Data will be collected to create treatment cascades associated with HIV, PrEP, HCV, MOUD, and STI testing, diagnoses, treatment, and care. Diagnoses and sero-conversion of HIV, HCV, and STIs will be assessed through medical history at every visit and via biological tests noted below. Based on diagnoses and current medications, time to linkage, initiation, or continuation of ART, PrEP, HCV, MOUD, or STI care and medications will be assessed from time of release from justice-based facilities, after randomization for those in the community, or upon diagnosis throughout the 12-month study participation period. Adherence to ART, PrEP, HCV, and STI treatments will be assessed using a visual analog scale (VAS [50]) for daily medications. Biological measures described below will assist with the evaluation of ART and PrEP adherence. For PLH at time of randomization the percent who maintain or achieve HIV viral load < 200 copies/mL at 6 months [51, 52] will be collected. Persistence on medication will be determined by assessing if medication was discontinued and reason for discontinuation, including successful cure of the infection if applicable. Attendance to medical visits will be confirmed with community providers and the MHU.

### Opioid and other substance use

The TCU drug screener [53] will be used to assess for opioid, stimulant, cannabis, synthetic cannabinoid, synthetic cathinone, hallucinogen, inhalant, and benzodiazepine use disorders at baseline, and months 6 and 12. History of substance use related treatment, including use of MOUDs, will be assessed at baseline. At each of the follow-up assessment visits, participants will be asked about current substance use and treatment adherence. Daily opioid and stimulant use, as well as route of administration, will be assessed using the timeline followback [54, 55]. At baseline, the Timeline Followback will ask about opioid and stimulant use for 30 days prior to justice involvement. Follow-up assessments will capture daily use throughout the intervention phase, and the last 30 days at the 12-month visit. Time to first opioid or stimulant use, number of days stimulants and/or opioids were used, and percent days abstinent will be assessed. Participants will also be asked about their experiences with opioid-related overdoses and naloxone use throughout the study period. Mortality and cause of death among participants will be tracked using the Center for Disease Control and Prevention National Death Index request system [56].

### Mental health, stigma, social functioning, pain, and quality of life

Pre-justice involvement mental health diagnoses will be collected. Current depressive symptoms will be assessed using the PHQ9 [57, 58] at baseline and months 3, 6, and 12. Social functioning, quality of life, and pain will be assessed using the PROMIS [59] at baseline and month 3, 6, and 12 visits. Stigma associated with being a person who uses or used substances will be assessed using a harmonized scale from the HIV Prevention Trials Network INTEGRA initiative (HPTN 094) at the same time points.

### Sexual and injection HIV risk behaviors

HIV risk behaviors will be assessed at baseline and follow-up research visits. Sexual and injection substance use behaviors will be assessed using the HIV Risk Behavior tool developed [60] for the National Institute on Drug Abuse’s Seek, Test, Treat, and Retain initiative [60].

### Biological measures

Biological assessments will be conducted throughout the project. These assessments include the following: (1) Rapid HIV testing will be done at baseline, at the end of the intervention (month 6), and at the end of the project (month 12) for those who are not living with HIV. For PLH, HIV viral load (VL) will be obtained from Quest Diagnostics or medical chart records at the same time points; (2) Rapid HCV testing will also be carried out at the baseline visit, those living with HCV will have HCV VL obtained from Quest Diagnostics at the time of release. Repeat HCV testing and VL will be done based on HCV status at months 6 and 12 post-release/enrollment. (3) Urine toxicology assessments for opioids, stimulants, and other substances (specific substances include: amphetamines, barbiturates, benzodiazepines, buprenorphine, cocaine, fentanyl, methadone, methamphetamine, opiates, oxycodone, and phencyclidine) will be done at baseline and months 3, 6 and 12 follow-up visits. (4) DBS and urine specimens will be analyzed to assess for adherence levels of tenofovir based PrEP and ART medications at months 3, 6, and 12 follow-up visits [61, 62]. (5) Gonorrhea, chlamydia, hepatitis B, and syphilis infections will be assessed at baseline and month 6 follow-up visits through urine or DBS analyses.

## Randomization

After eligibility has been determined and informed consent has been obtained, the participant will undergo the baseline assessments and biological tests outlined above in Table 1. Once these have been completed, the participant will be randomized by a research staff member. Simple randomization stratified by project site will be allocated via the REDCap randomization module. Allocation tables were developed by the project Statistician using computer based random number generation. Participants will be assigned to one of the two following groups: Group A, participants assigned to this group will receive help from a PN who will connect them to treatment providers in their local community and Group B, participants assigned to this group will receive care from a project-supported MHU. The participant will be told immediately if they are randomized to receive PN or MHU services.

## Interventions

### Patient navigation (PN) arm

Our PNs will be individuals that ideally have “shared living experiences” (e.g., HIV or history of SUD treatment) with participants and will help them overcome barriers to accessing and engaging in quality care [15]. We will work with our community partners to assure that our PNs are integrated as members of the community health care teams. The PN will work closely with the study participants to access medication for opioid use disorders, behavioral health for stimulant use and other SUDs, HIV and HCV testing, prevention, and treatment, as well as other primary health care. They will also assist with housing, health insurance, transportation, childcare, and other needs during the six-month intervention. Across all four community sites, ACTION PNs will receive active, comprehensive training and guidance on providing appropriate linkage to community services including harm reduction services such as syringe services programs in Connecticut (not available in Texas) and education on safe injection practices of substances to reduce HIV and HCV infection and reinfection.

The community partners collaborating on this project have extensive experience in PN support services, their PN protocols will provide a guiding framework for the ACTION training protocol. PN training will capitalize on existing linkages to an array of services through Federally Qualified Health Centers or similar organizations, including primary care, substance use treatment, behavioral health, case management, and care coordination. In addition, these services include confidential rapid HIV and HCV testing, education about prevention of HIV and HCV care, PrEP, post-exposure prophylaxis for HIV, and MOUD (buprenorphine and extended-release naltrexone). All PNs will be trained to provide motivational interviewing and goal setting as part of their services provided in the project as it has been shown to improve treatment engagement in persons who use substances [63, 64].

### Mobile health unit (MHU) arm

MHUs in the four project areas will either operate and provide care directly on the MHU. All MHUs will provide on-site integrated HIV, HCV, and substance use testing, prevention, diagnosis, treatment, and care. When medications are not able to be provided on the MHU, a clinician on the MHU (or via referral) will provide prescriptions for any medications related to their care, including MOUD (buprenorphine/naltrexone and extended-release naltrexone). Furthermore, the MHU team will have an established relationship with Ryan White Qualified Healthcare programs and other community organizations for linkage to services in the community they are not able to provide directly. A community health worker (CHW) will be on the MHU and will assist in referring and linking participants to community-based services as needed.

Prior to the end of the six-month intervention period, study staff will work to transition participants randomized to the MHU arm to either another MHU that is convenient to them or other community-based services in order to maintain continuity of care. Protocols have been developed in each of the communities in Connecticut and Texas to identify community locations in which to locate the MHUs that will be accessible by the target populations.

## Compensation

Participants will be compensated for their time completing research-related study visits. Upon completion of the baseline assessment (including biological testing) participants will be compensated $50. Follow-up visits conducted 1- and 3-months post-release/enrollment will be compensated at a rate of $50 per completed research visit. Research visits at month 6- and 12- post-release/enrollment will be compensated at $75 per completed research visit. To increase retention, a payment of $5 will be given if the participant is successfully contacted during the months without scheduled follow-up visits which will be conducted to optimize retention. All payments will be in the form of gift cards. To reduce the risk of coercion among those involved in the justice system payment will be given to the participant upon re-entry to the community for those who undergo a research visit in a justice facility.

## Collection and reporting of adverse events

Any unfavorable and unintended sign (including an abnormal laboratory finding), symptom or disease temporally associated with the use of a medical treatment or procedure, regardless of whether it is considered related to the medical treatment or procedure will be noted as an adverse event. All project staff will be trained to recognize, document, and report adverse events. Each adverse event will be classified by the PIs as serious or non-serious and classify each adverse event according to the attribution categories. Each of these adverse events will be graded as (1) mild, an experience that is transient, and requires no special treatment or intervention; (2) moderate, an experience that is alleviated with simple therapeutic treatments, an experience impacts usual daily activities. Or (3) severe, an experience that requires therapeutic treatments or hospitalization. Serious adverse events include events that result in death, serious injury, a life-threatening experience, inpatient hospitalization, persistent or significant disability/incapacity, termination of employment, or institutionalization in residential treatment, hospital, or jail. Adverse events will also be assessed for attribution of the project as (1) not related, the adverse event is clearly not related to the study procedure; (2) possibility related, an event that follows a reasonable temporal sequence from the initiation of study procedures, but that could readily have been produced by other factors; and (3) related, adverse event it clearly related to the project. Any event or outcome that was not described as a risk of participation in the research or, even though described as a risk, which has occurred with unexpected severity or frequency will also be monitored and systematically assessed.

In the event that a participant either withdraws from the study or the investigators decide to discontinue a participant due to a serious adverse event, the participant will be monitored by the PIs via ongoing status assessment until (1) a resolution is reached (e.g., the problem requiring hospitalization has resolved or stabilized with no further changes expected); (2) the serious adverse event is determined to be clearly unrelated to the study intervention; or (3) the serious adverse event results in death.

Adverse events expected to be deemed serious will be reported to the Yale Contact PI ([name]) within 24 h of detection. If deemed serious, the PI will send a full report on the serious adverse event, including the action taken with regard to continued study participation to the sIRB and DSMB within 3 business days. Non-serious adverse events that lead to participant removal from the protocol will be reported to the sIRB and DSMB within 7 business days. The PI will maintain a record of the serious adverse event, which can be provided to the sIRB electronically. The outcome of serious adverse events also will be reported to National Institute on Drug Abuse in annual progress reports.

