HCV cascade of care cascade will be assessed as the proportion who have a reactive rapid point of care HCV test with confirmatory reflex HCV VL; the time to linkage for and HCV treatment appointment, and time to receiving HCV direct acting antiviral treatment during the 6 month intervention; the proportion eligible who complete treatment; of those, the proportion who achieve sustained virologic suppression at week 12 (undetectable HCV VL); and of those who achieve sustained virologic suppression [70, 71], the proportion who have HCV re-infection at 12 months. The HCV care cascade will be calculated overall and stratified by arm.

OUD/SUD outcomes and cascades of care will include the proportion who have a current or past diagnosis of SUD (including stimulant and opioid use) by (a) proportion of monthly negative versus positive/missing urine samples, (b) self-reported days of opioid and injection drug use using the timeline followback and other drugs and alcohol using the TCU Drug Screen 5 and Opioid Supplement [53], and c) and percent of opioid and/or stimulant-free months (0–6). In addition, we will track non-fatal and fatal overdose events, addiction treatment participation, and linkage to and retention on MOUD using a brief version of the Treatment Services Review [72] that records type and dose of MOUD and behavioral health. These cascades will be calculated overall and stratified by arm.

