#### Data safety monitoring board

A Data Safety and Monitoring Board (DSMB) will be assembled in order to monitor adverse events that could occur during the research. Members of the DSMB will include at minimum a representative from criminal justice, a health service provider, a behavioral health provider, and a biostatistician. The DSMB will meet initially before the start of the trial to discuss the protocol, approve the commencement of the trial, and to establish guidelines to monitor the study. A Chair of the Board will be selected at the initial meeting. Meetings of the DSMB will be held two annually at the call of the Chair. An emergency meeting of the DSMB may be called at any time by the Chair should questions of client safety arise. All meetings shall be closed to the public because discussions may address confidential patient data. The DSMB meetings will consist of an open and a closed session. The open sessions may be attended by the PIs and other study staff but should always include the study biostatisticians. Issues discussed at open sessions will include conduct and progress of the study, including client accrual and problems encountered. Participant-specific data and treatment group data may not be presented in the open session. The closed session will be attended only by voting DSMB members and administrative support staff not otherwise affiliated with the study. Others may be requested to attend by the DSMB (e.g., study statistician). All safety and efficacy data are and must be presented at this session. The discussion at the closed session is completely confidential. Should the DSMB decide to issue a termination recommendation, full vote of the DSMB will be required. In the event of a split vote, majority vote will rule and a minority report should be appended.

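### The adverse-event definitions make safety counts depend partly on linkage to care, so the by-arm data the DSMB sees could be biased in a direction that cannot be known in advance

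*Protocol article*

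**What the plan says.** All of the rules are in the section on collection and reporting of adverse events.

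- An adverse event is "Any unfavorable and unintended sign (including an abnormal laboratory finding), symptom or disease" that is "temporally associated with the use of a medical treatment or procedure, regardless of whether it is considered related to the medical treatment or procedure".
- The seriousness list opens conventionally: "Serious adverse events include events that result in death, serious injury, a life-threatening experience, inpatient hospitalization". It ends with "termination of employment, or institutionalization in residential treatment, hospital, or jail". No sentence addresses planned, voluntary or study-facilitated treatment entry.
- A further clause covers events or outcomes not described as a risk, or a described risk "which has occurred with unexpected severity or frequency will also be monitored and systematically assessed". It requires no link to treatment.

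Elsewhere, the study design section lists SUD treatment, including MOUD, among the services of the trial. Navigators refer participants to community providers, while the MHU arm gives clinical care on board. The analytic plan follows "addiction treatment participation, and linkage to and retention on MOUD" as outcomes by arm. For the closed DSMB session, the article states: "All safety and efficacy data are and must be presented at this session".

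**The concern.** The wording reads as if taken from a trial of a medical product, where every participant receives a treatment and an adverse event can be anchored to it. Here the interventions are two ways of connecting people to treatment. This has two consequences.

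First, whether an event qualifies as adverse can depend on whether the participant has used medical treatment, and the arms are expected to differ in that. Take an illness in someone who was never linked to care. Whether it is recorded turns on how staff read an undefined phrase.

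Second, seriousness can depend on access to care. A relapse that leads to residential treatment meets a seriousness criterion; the same relapse left untreated need not. Residential treatment is also part of the SUD care that the trial promotes and measures as an outcome.

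At stake is the by-arm safety information available to a board that can recommend termination. Custody, which the article expects (it plans follow-up in custody and possible adjustment for incarceration time), could also sit in the same tally as deaths and hospitalizations.

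**Working it through.** The article gives no adverse-event rate, safety power or by-arm safety figure, so there is nothing to reproduce. The point rests on the text; the arithmetic only shows how large the dependence could be and whether its direction is fixed.

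**Step 1: the passages side by side.** An adverse event needs a temporal tie to medical treatment, and the primary outcome is time to starting a medical treatment. Residential treatment is a seriousness criterion, and SUD treatment is a delivered service and a measured outcome. Nothing in the article says which role takes precedence when one occurrence fits both.

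**Step 2: the treatment-tied definition, read at its most literal.** Inputs from the sample size section: 5% PLH and 95% at risk; PrEP uptake 10% (PN) and at best 20% (MHU); ART uptake about 51% and 64%. With 864 randomized 1:1, there are 432 per arm.

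- PN uptake: 0.95 × 0.10 + 0.05 × 0.51 = 0.1205; 432 × 0.1205 ≈ 52 people.
- MHU uptake: 0.95 × 0.20 + 0.05 × 0.64 = 0.2220; 432 × 0.2220 ≈ 96 people.
- Ratio: 0.2220 / 0.1205 = 1.84.

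Suppose only people on PrEP or ART could generate a counted event, and the true event rate were equal in both arms. The expected counts are then:

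| Assumed true rate | PN | MHU |
|---|---|---|
| 10% | 5.2 | 9.6 |
| 20% | 10.4 | 19.2 |
| 30% | 15.6 | 28.8 |

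This is an extreme reading. If the study's own tests, scheduled for everyone, count as a medical procedure, the ratio returns to 1.

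**Step 3: jail and residential treatment as seriousness criteria.** Here the list is read broadly, with every jail episode and every residential admission counted. Let *u* be the proportion linked (the Step 2 uptake is used as a stand-in, since the article gives no SUD linkage rate), *b* the jail risk if not linked, *r* the multiplier on that risk if linked, and *q* the residential admission risk among those linked, taken as independent of jail. The SAE proportion in an arm is

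p(u) = b(1 − u) + u[1 − (1 − rb)(1 − q)],

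and the MHU minus PN difference is (0.2220 − 0.1205) × {[1 − (1 − rb)(1 − q)] − b}.

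Assumed ranges: b = 20%, 30%, 40%; q = 5%, 10%, 20%; r = 1, 0.75, 0.5. This gives nine combinations for each r.

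| r | Range of difference (percentage points) | Combinations below zero |
|---|---|---|
| 1 | +0.30 to +1.62 | 0 of 9 |
| 0.75 | −0.66 to +1.22 | 4 of 9 |
| 0.5 | −1.62 to +0.81 | 7 of 9 |

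Worked extremes:

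- b = 0.20, q = 0.20, r = 1: 0.1015 × (0.36 − 0.20) = +0.0162.
- b = 0.40, q = 0.05, r = 0.5: 0.1015 × (0.24 − 0.40) = −0.0162.

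A difference of 1.62 points is about 7 participants out of 432. If linkage leaves jail risk unchanged, the better-linking arm shows more SAEs; if linkage lowers jail risk, the sign often reverses.

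Steps 2 and 3 rest on different readings of the definition (strict and broad), so their effects should not be added together.

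**The case against.** The strongest reply is that the text is narrower than it first appears. An adverse event must be unfavorable and unintended, and an SAE is an event that *results in* institutionalization. A reader might infer that entering residential treatment is itself scored as a serious harm. On a strict reading it is not, when the entry is intended. Likewise, re-incarceration alone is not a sign, symptom or disease, so it does not follow that every return to jail is an SAE.

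A reader might also infer that harm in people never linked to care goes unrecorded. The article does not support that either. The tie to treatment is temporal, not causal. Table 1 schedules overdose and adverse-event questions at months 1, 3, 6 and 12 for all participants, deaths are traced through a national death index, fatal and non-fatal overdoses are tracked separately, and the clause on unexpected events needs no treatment link.

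Further, no between-arm SAE test or count-based stopping rule is stated, attribution includes a not-related category, and the DSMB decides the content of its reports. Counting jail and job loss as serious may be deliberate caution in this population. Any criterion based on level of care, hospitalization included, depends somewhat on access.

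Most of this stands, and it limits the problem. It does not remove it. A relapse or other unfavorable event that leads to residential care still becomes serious through access to care. Unlike hospital admission, SUD treatment is something both arms set out to deliver. The not-related category does not take an event out of the SAE count. The overdose and death data leave the definition of the other counted events unchanged.

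**Conclusion.** The point holds as a poor fit between the stated safety definitions and a linkage trial: by-arm adverse-event and SAE counts would depend partly on linkage and could mislead the DSMB. The tempting conclusion that the better-linking arm will look less safe is not supported. Jail and job loss may fall with better linkage, both arms are active linkage arms, and the SAE illustration runs from +1.6 to −1.6 percentage points.

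The actual size is unknown. The 1.84 ratio rests on the article's planning uptake and on an extreme reading of the definition. Every event rate, the jail multiplier, and the use of PrEP/ART uptake to stand for SUD linkage are assumptions. The case for change is that the ambiguity is real and inexpensive to remove, not that a bias of known size or direction has been shown.

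**What to change.** 1. In the adverse-event section, define an adverse event as an unfavorable event occurring after randomization in any participant, whether or not a medical treatment or procedure was used.
2. State that planned or voluntary entry into SUD treatment is not in itself an SAE, so that this section agrees with the study design section and the cascade outcomes.
3. Keep jail, job loss and residential admission reportable as they are now, but in the DSMB report tabulate them by arm separately from medical SAEs (death, life-threatening event, hospitalization, disability).

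The cost is revised protocol and form wording, plus recoding of events already recorded so that one definition applies throughout. No new data collection is needed, and present sIRB and DSMB notification is unaffected.
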